## Abstract

**Introduction:**

Given the unprecedented increase of long-term care and aging in place demand, informal caregivers are exposed to higher levels of stress (the caregiver’s burden) with negative repercussions on their physical and mental health and additional human and economic costs for the National Health Systems. The DanceCARE method offers an innovative and blended intervention based on a body–mind approach that was co-designed by dance-movement therapists, body–mind experts and aging care researchers to alleviate the burden on informal caregivers of older people. The purpose of the paper is to describe the detailed procedure of the pilot study.

**Method:**

This mixed-methods pilot study aims to measure the impact of the original DanceCARE intervention on the perceived burden and depression levels of 90 informal and semi-formal caregivers living in Greece, Italy and Spain, and the quality of life of older care receivers. Validated psychometric scales, qualitative interviews, and art-based/embodied research methodologies were adopted.

**Results:**

The pilot study will be the first implementation of the DanceCARE intervention, aiming to investigate the feasibility and preliminary effects of the method. This article therefore illustrates the research protocol starting from the main research question and explains the target groups, the pre and post-pilot research phases, the tools that will be used and the resources to employ, including human resources, the time-lines and the methodologies to use uniformly in Italy, Greece, and Spain.

**Discussion:**

The novelty of DanceCARE lies in the body–mind intervention paired with a multi-component assessment methodology that can provide evidence of the efficacy of body–mind interventions that are still under-investigated.

## Introduction

1

The study is part of the DanceCARE project “Dance Movement Therapy and Conscious Movement as innovative tools in emotional education and support for long-term caregivers” funded by the Erasmus + programme (contract 2023-1-IT02-KA220-ADU-000154702), and aimed to design an original body–mind educational intervention and test it with informal and semi-formal caregivers of older persons with long-term care (LTC) needs in Greece, Italy and Spain.

According to the World Health Organization (WHO) reports, the number of care-dependent people worldwide is increasing every year, and a large percentage (almost 29%) of them are over 60. Co-existing chronic diseases are often associated with the need for health and social care for older adults. Moreover, the European Union’s LTC report (2021) underlines that ensuring sufficient numbers of qualified formal caregivers, i.e., social and healthcare professionals and providing support to informal caregivers, i.e., family members and friends of older people are key challenges in the European aging society. LTC systems are differently structured and developed across Europe, but what all these systems have in common is the predominance of women caregivers in both formal and informal sectors (Wimo et al., 2017).

In many Western countries, particularly those in the Mediterranean region, which are characterized by a family-centered care model (Theobald and Luppi, 2018), in addition to formal and informal services, migrant care workers live with families—namely, private healthcare providers and live-in carers who almost always come from migrant backgrounds and may or may not have a regular employment contract (Stenberg and Hjelm, 2023). They often have not received any training in caring for older adults, but perform daily care and home assistance activities (such as personal hygiene, feeding assistance, and administering medication) that would normally be carried out by professionals in the formal care sector, such as those working in elderly care facilities (Santini et al., 2025). Due to this ambiguity, (migrant) family care assistants can be considered semi-formal caregivers. Live-in migrant family care assistants often experience sleep disorders (Vianello, 2023) financial insecurity, excessive working hours (as many of them live with the elderly person they care for 24 h a day), and social isolation, which compounds the stress associated with their care work and leaves them highly vulnerable (Ulitsa et al., 2025) and lead to poor mental health, e.g., depression and anxiety (Hasan et al., 2021).

By taking both informal and semi-formal caregivers into account, even though they have different motivation to care, and different backgrounds, we take on the challenge of fostering inclusion and building a bridge between these two groups, offering an educational tool that engages them emotionally and encompasses various areas of care. By connecting these two types of caregivers, it is also potentially possible to address the need to match the supply and demand for care.

In general, LT caregivers (both informal and semi-informal) are aging, most of them being middle-aged: a Europe-wide analysis reports that in most countries informal (non-professional) caregivers are between 48 and 53 years old on average (Peña-Longobardo and Oliva-Moreno, 2022). They perform a large part of LTC in most Member States, with important implications for them, the people they care for, and society at large. Both informal and semi-formal care is demanding, and LT informal caregivers are often isolated and at higher risk of psychological distress and depression. Caregiver burden is a specific form of stress (Kim et al., 2012; Lindt et al., 2020) that tends to become chronic the longer the caring situation lasts and manifests itself in the most diverse and subjective forms as sleep and appetite disturbances, depressed mood, and difficulties with concentration and memory, irritability and anxiety, persistent worry, somatization symptoms, such as body ache, and increased susceptibility to illnesses (Bom et al., 2019; Del-Pino-Casado et al., 2019; Greenwood et al., 2018; Mohanty and Niyonsenga, 2019; Pignatiello et al., 2022; Pinquart and Sörensen, 2011). Literature indicates that caregivers who prioritize their own well-being, understand their emotional limits and resources, and avoid isolation by engaging in peer support, are more likely to experience better physical and mental health, leading to less reliance on drugs and healthcare services and improved care for the older person they are looking after (Søvold et al., 2021; Parr and Mielenz, 2023).

Focusing on informal and semi-formal caregivers’ burden and the risk of developing psychological disorders, the scientific community has long discussed the concept of ‘embodied cognition’ and the need to put bodily processes at the center of education, care and mental health (Foglia and Wilson, 2013; Shapiro, 2019). Embodied cognition is a concept that defines the body (sensations, actions and bodily experiences) as a basis for our understanding of the world, the construction of conceptual knowledge, as well as meaning formation (Fincher-Kiefer, 2019; Maes et al., 2014; Varela et al., 1991). Unlike traditional cognitive science, which views the brain as a computer processing symbols, embodied cognition emphasizes a holistic view where the body, environment, perception, and action are all interconnected generating thoughts to emerge. Embodied cognition challenges the idea that cognitive processes are solely about symbol manipulation and abstraction, arguing that many cognitive functions, like perception and understanding, are grounded through the body and arise from direct physical interactions and experiences (Gallese, 2001; Damasio, 2000). This theory has significant implications for understanding learning, language acquisition, social interaction, and even the design of educational tools and methods, where physical actions and experiences can enhance cognitive outcomes. From this perspective, it could be argued that there is no comprehensive intervention if it does not also take the body into account. This concept is slowly spreading and DanceCARE represents a valuable step towards a paradigm shift, responding to the need to reduce the burden of care through body–mind methodologies.

Although there are some encouraging studies demonstrating the potential of body–mind techniques in combating stress and improving mental health and well-being in the adult population (Bräuninger, 2012; Esmail et al., 2020; Rodríguez-Jiménez et al., 2022) there are few studies focusing on informal and semi-formal caregivers of older adults (e.g., Champagne, 2024; Fontanesi and Newman-Bluestein, 2024) and studies supporting a blended online approach for mind–body interventions are also limited and very recent (Blanc et al., 2025; Shim et al., 2024). The DanceCARE protocol was designed to fill this knowledge gap by investigating whether and how a body–mind educational intervention can mitigate the burden and reduce the risk of depression of informal and semi-formal caregivers of older people with LTC needs.

The project aims to provide tools for well-being, care, and health to informal and semi-formal caregivers through Dance Movement Therapy (DMT) and WiseMotion^1^ (WM) methodologies, which have already proven effective in regulating the psycho-emotional stress to which such work inevitably leads. DMT is the psycho-therapeutic use of movement to promote the emotional, cognitive, physical, and social integration of an individual. Grounded in the interconnections of body and mind, DMT uses purposeful movement and creative expression to foster self-awareness, emotional regulation, and resilience (Payne, 1992). Research has shown that DMT is effective in reducing psycho-emotional stress, alleviating symptoms of depression and anxiety, and enhancing overall well-being in both clinical and care-giving populations (Chaiklin and Wengrower, 2015; Pylvänäinen et al., 2015; Karkou et al., 2019). WM is a movement method based on neuroscientific understanding of the bodily and brain functions (Porges, 2009). WM utilizes embodied exercises that combine body awareness, emotional expression, creativity and social interaction to enhance psychological well-being and brain health (Poikonen et al., 2024). Previously, WM has been applied for people with multiple sclerosis disease or dementia, and people recovering from stroke. Both methods emphasize that the first need of a caregiver is to know how to take care of oneself, to have a good awareness of one’s emotions and behavioral reactions, to know how to handle anger, frustration, sadness, stress, and to have a good sense of self.

## Materials and methods

2

### Study design

2.1

The main aim of the study is to examine the feasibility of the innovative, blended, and flexible educational program based on DMT and WM methodologies. The second aim is to check if and how the application of key body–mind methodologies contribute to the reduction of burden, depression and isolation of informal and semi-formal caregivers, and at the same time to the increase of the quality of life of older care takers. The study wants to answer the following main research questions “Is the DanceCARE intervention feasible to implement in terms of recruitment, retention, adherence, and acceptability?” and “To what extent and how can the DanceCARE intervention change the perceived burden and depression levels of semi-formal and informal caregivers of older people with long-term care needs?”

Other research questions include whether the intervention also improves the quality of life of the older person receiving care, and whether the blended approach—which involves support through short online videos—is considered helpful and effective by the participants.

To answer these questions, this pilot convergent mixed-method study, chosen in preparation of a future full-scale study, integrates standardized quantitative instruments for measuring perceived levels of burden and depression, with diverse qualitative approaches to capture the complexity of human experience, e.g., interviews, focus-groups and live observations of participants during the body–mind sessions, enriched by art-based and embodied research approach (Hervey, 2000).

These qualitative data will not be limited to verbal accounts; they will also include symbolic and metaphorical expressions emerging from arts-based and embodied practices, which remain grounded within the qualitative paradigm and allow for a process-oriented understanding of participants’ experiences rather than capturing them at a single point in time.

Quantitative and qualitative datasets will be analyzed separately, and the results will then be merged during the interpretative phase. At this stage, aggregate statistical findings will be integrated with qualitative insights, including both quotations derived from interview transcripts and themes identified through the analysis of arts-based and embodied materials. In line with a convergent mixed-methods design, this integration will involve the systematic comparison and triangulation of quantitative and qualitative results, through strategies such as joint displays and interpretative weaving, to identify points of convergence, complementarity, or divergence (Fetters et al., 2013). This integrative process will enable a more nuanced and comprehensive understanding of participants’ experiences with the intervention, combining verbal accounts with symbolic and embodied expressions.

The study foresees three data collection waves: at the baseline (T0) i.e. 3 months before the start of the training; at mid-time, i.e., after the fourth intervention session (T1), and within 2 weeks from the conclusion of the intervention (T2). The three phases of data collection are described in Figure 1.

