**Figure 1 fig1:**
[figure not shown]
Study design with timeline.

In the pre-pilot phase, caregivers will be contacted by researchers and screened by phone according to the inclusion criteria (see par 2.2.1.). If the recruited person meets the inclusion criteria, they are included in the sample and they receive the online questionnaires (see Appendix 1) and the informed consent. Contextually, during the phone call, the researcher and the interviewee agree to a face-to-face meeting during which the informed consent is given back signed to the researcher. The latter asks for the possibility of also speaking with the older care recipient, if they are able to answer a very brief interview. Between the screening and the T0 the researcher receives and reads the questionnaire compiled online by the caregiver. At the baseline (T0), the researcher administers the face-to-face interview (see Appendix 2) starting from the answers that the caregiver gave to the questionnaire. When it is possible also the care receiver is interviewed. In the intermediate phase (T1), caregivers and body–mind trainers are briefly interviewed with the aim of understanding whether the activities are liked and effective and whether adjustments need to be made. In the post-intervention phase (T2), the caregivers are asked to answer the questionnaire (containing the same dimensions explored in T0 except for the socio-demographic data) and to participate in a second interview. In this phase, the 15 older adults are interviewed again.

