Prior to the pilot phase, a small group of professionals—comprising two or three representatives from each country involved in the pilot project (hereinafter referred to as “mind–body trainers”)—will undergo specialized training, based on the aforementioned guidelines, on the intervention to be carried out with informal and semi-formal caregivers. All body–mind trainers have a background in DMT and are licensed through an institution recognized by the European Association of Dance Movement Therapy. All selected DMT trainers have on average over 5 years of work experience and are registered with national dance therapy associations.

Also, to ensure effective monitoring, each session will be attended by an observer—either a therapist specializing in DMT or a trainee selected at the national level through relevant associations and institutions. The observer will be provided with project guidelines, previously translated in the national language, for observing the body–mind sessions, thereby contributing to the collection of high-quality art-based and embodied material.

The intervention for the caregivers consists of 1 h and a half weekly face-to-face activities based on the DMT and WM techniques previously identified and developed in group for stimulating communication and peer networking, thereby counteracting isolation and the exacerbation of stress and other symptoms such as depression (Lauritzen et al., 2015). The frequency of the body–mind sessions has been defined during the construction phase of the programme through expert advice, but also through the collection of opinions of the caregivers themselves.

As shown in Figure 2, at each of the three pilot sites, 30 informal caregivers will be divided into three groups of up to ten participants, who will attend the program simultaneously on different days and at different times of the week for approximately 3 months, taking into account holidays and other factors that could slightly affect the timeline.

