### Data management and analysis

2.5

The analysis plan for quantitative data includes a description of outcomes. The normality of continuous variable distributions will be assessed using the Shapiro–Wilk test. Depending on the results, data will be presented as either mean and standard deviation (for normally distributed variables) or median and inter-quartile range (for non-normally distributed variables). Categorical variables will be described using absolute frequencies and percentages. Comparisons between outcomes and exposures will be performed as follows: Chi-square tests for categorical variables; *t*-tests or one-way ANOVA for comparisons involving normally distributed continuous variables across groups; and non-parametric tests such as the Wilcoxon rank-sum test or Kruskal–Wallis test for non-normally distributed continuous variables. Correlations between continuous variables will be assessed using either Pearson’s or Spearman’s correlation coefficients, depending on the distribution. Although the primary aim of the study is assessing the intervention feasibility, in addition to *p*-values, effect sizes will be calculated and reported to quantify the magnitude of observed differences and associations, even if they are not statistically significant. In addition, in the absence of a control group, effect sizes for within-subject changes (pre–post) will be calculated (e.g., Cohen’s *d* for paired samples) to quantify the magnitude of change over time. These estimates will support the interpretation of the practical relevance of the findings, although causal inferences cannot be established.

Temporal comparisons (T0 vs. T2) will be conducted using paired-sample *t*-tests. If significant differences are identified in univariate analyses, multivariate models will be considered. Results will be reported as coefficients with standard errors (for continuous outcomes) or odds ratios with 95% confidence intervals (for binary outcomes), as appropriate. Model fit will be evaluated using *R*-squared or pseudo *R*-squared values.

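### The only pre-intervention burden and depression scores are taken about 3 months before session 1, so roughly half or more of the T0–T2 interval is untreated time

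*Protocol article*

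**What the plan says.** Section 2.1 of the protocol article defines baseline by this timing: "at the baseline (T0) i.e. 3 months before the start of the training". T1 follows the fourth session, and T2 comes no later than 2 weeks after the programme ends. Under Figure 1, the same section describes how the baseline form is returned: "Between the screening and the T0 the researcher receives and reads the questionnaire compiled online by the caregiver". The scores are therefore no closer to session 1 than the T0 meeting is.

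Table 3 and section 2.4.1 give ZBI, CBI and BDI at T0 and T2 only. T1 holds short interviews and satisfaction items.

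Section 2.5 sets the analysis: "Temporal comparisons (T0 vs. T2) will be conducted using paired-sample" t-tests. Because there is no control group, within-subject pre–post effect sizes such as Cohen's d for paired samples are added, with the caveat that causality cannot be established. Section 3.2 sets the expected reductions (ZBI by at least 10 points, CBI by 10–20%, BDI by 17.5%) at T2 against the same baseline.

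On programme length, section 2.3 and Table 2 give seven group sessions. Section 2.3 describes them as "1 h and a half weekly face-to-face activities", and also has the groups attend "for approximately 3 months, taking into account holidays and other factors that could slightly affect the timeline".

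**The concern.** The second main research question asks how far the intervention changes burden and depression. The contrast meant to answer it starts about 3 months before anyone is exposed. Whatever happens to caregivers while they wait is added to whatever happens during the programme, and no intermediate measurement exists to separate the two.

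Two mechanisms can act in that wait, in opposite directions. Caregivers enter on a high self-rated stress score (section 2.2 and Table 1), so their burden and depression scores may drift back towards average without treatment. On the other side, the Introduction says caregiver burden tends to become chronic as caring continues, so untreated scores could rise and mask a benefit.

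The study is described as preparation for a full-scale study. An effect size that covers the wrong window would carry over into that planning.

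**Working it through.** The protocol states no T0–T2 interval and no share of it, so there is no figure of its own to reproduce.

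**Inputs**
- Gap from T0 to session 1: 3 months (section 2.1) = 3 × 52.1775/12 = 13.04 weeks.
- Programme length: about 3 months (section 2.3) = 13.04 weeks; or seven weekly sessions, which span 6 weeks from first to last, or 7 weeks if counted as full weeks.
- Lag from programme end to T2: 0 to 2 weeks (section 2.1).

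**Untreated share of the interval** = gap / (gap + programme + lag)

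| Programme | Lag 0 weeks | Lag 2 weeks |
|---|---|---|
| 3 months | 13.04/26.1 = 50% | 13.04/28.1 = 46% |
| 7 weeks | 13.04/20.0 = 65% | 13.04/22.0 = 59% |
| 6 weeks | 13.04/19.0 = 69% | 13.04/21.0 = 62% |

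The range is 46–50% on the stated 3 months and 59–69% on a weekly schedule. The online form is returned before the T0 meeting, so the true gap may be slightly longer.

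**What this means for the score.** The share of the score change does not follow from the share of time. Suppose a 10-point ZBI fall is seen from T0 to T2. If the change before session 1 were −3, 0, 2, 5 or 8 points (positive = fall), the pre-start part would be −30%, 0%, 20%, 50% or 80%. Nothing in the protocol selects among these.

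**Regression to the mean, illustration only.** Spurious fall = (mean shift of the selected group, in SD of the ladder) × (drop in the ladder–ZBI correlation from T0 to T2) × (ZBI SD). All inputs are assumptions: 30–80% of screened caregivers pass the stress cut; the correlation is 0.5–0.6 at T0 and 0.3–0.5 at T2; the ZBI SD is 12–18. The result is 0 to 0.35 SD, or 0 to about 6 ZBI points. Zero arises when the correlation does not fall.

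**Effect of a repeat one week before session 1.** With a gap of 1 week in the same formula, the 3-month programme gives 1/(1 + 13.04 + 2) = 6% to 1/(1 + 13.04) = 7%. The weekly schedule gives 1/(1 + 7 + 2) = 10% to 1/(1 + 6) = 14%.

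**The case against.** The best defence is that the protocol claims little. Feasibility is the main aim (section 2.1), the study is exploratory and tests no predefined hypotheses (section 2.2), and sections 2.5 and 3.3 acknowledge the missing control group. No decision rule hangs on the ZBI change, and an uncontrolled pilot stays non-causal whatever the baseline date. This stands as a limit on severity. It does not cure the timing: lacking a control group is a design limitation, whereas an early baseline is a separate and avoidable defect, and neither section mentions it. The mitigation in section 3.3, using several measures, does not help because all three scales share the same T0.

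Stronger readings are tempting, and the document does not support them:
- A reader might infer that half of the T0–T2 *change* is untreated drift and regression to the mean. The arithmetic gives shares of time only. Change need not accrue evenly, regression to the mean is not proportional to elapsed time, and drift may go either way.
- A reader might infer that losses before session 1 are pooled with drop-out from the programme. No passage says so; section 2.4.1 lists recruitment, retention and attrition, and adherence, and how early losses are classified may be set elsewhere.
- A reader might think the T0 questionnaire could be moved next to session 1 at no cost. The T0 interview starts from the questionnaire answers (section 2.1), so either that link breaks or the interviews move too.

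Figure 1, the timeline, was not visible in the text available for this review, so whether it qualifies the 3 months could not be checked. The sentence in section 2.1 is explicit.

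**Conclusion.** The point holds as a timing defect. The sole pre-intervention ZBI, CBI and BDI scores lie about 3 months before session 1, so 46–50% of the T0–T2 interval is untreated on the stated 3-month programme, and 59–69% if the seven sessions run weekly. These figures rest only on the protocol's own timings. The paired test, the pre–post effect size and the expected reductions all use this contrast, and even read descriptively it does not measure change over the intervention.

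The size and sign of the resulting distortion are unknown; the 0 to 6 ZBI points for regression to the mean are assumption-based, and the conclusion does not depend on them. The protocol's caveats about causality keep this from being critical. It should be fixed before the sessions begin, because the missing measurement cannot be recovered afterwards.

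**What to change.** 1. Keep T0 and its interview as planned. Resend the online ZBI/CBI/BDI form, without an interview, in the week before session 1 (T0b).
2. Make T0b–T2 the contrast for the paired comparison and the pre–post effect size, and refer the expected reductions in section 3.2 to it.
3. Report T0–T0b descriptively as change before the intervention, per unit of time if set beside T0b–T2, because the two periods may differ in length. State that this does not replace a control group and that some regression to the mean may continue after T0b.
4. Do not use the difference (T2 − T0b) − (T0b − T0) as an effect measure. It compares periods of possibly unequal length and puts early regression to the mean into the comparison period. With equal variances and correlations its variance is 6σ²(1−ρ) against 2σ²(1−ρ) for a simple difference, so its standard error is √3 = 1.73 times as large.
5. Separately, reconcile seven weekly sessions with the stated duration of about 3 months in section 2.3, since this fixes the exposure window.

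Cost: one more online completion of 22 + 24 + 21 = 67 items per caregiver, some added burden on people who are already stretched, possibly some missing T0b forms, and a short amendment. No visit or interviewer time is needed.
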